#### 8.7.4.5 Location of household and issuance of study ID card

A detailed route description to locate the household of the participant including sketching of a map will be taken, to aid the planned spot checks to assess uptake of PMC at home. Lastly a subject's identification card will be issued. A GPS will be used to collect the exact location of the participant's house.

#### 8.7.5 **Unscheduled visits (passive follow-up)**

##### 8.7.5.1 Inter-current illness

A passive surveillance system will be used to monitor inter-current illnesses through the research clinic. Parents will be instructed to bring their child to the research clinic for any suspected illness. The 'problem' (reason for attending the clinic during passive surveillance) and 'diagnosis' will be recorded using a standard list based on the International Classification of Disease (ICD-10) for children [18]. Blood samples for malaria smears, haemoglobin and dried blood spot on filter paper will be taken if clinically indicated.

Information regarding economic costs will also be collected during this visit. Provider costs such as time spent for registration, time spent with the nurse and time spent with a physician will be measured. In addition, all equipment usage and medicines will be identified and retrospectively costed using unit prices. Economic costs to the patient will also be collected; costs regarding travel time to the facility, travel costs, waiting time, among others.

##### 8.7.5.2 Verbal autopsy visit

All parents of children who die will be advised to report the incident to the study clinic/study staff/HSA as soon as possible for a detailed verbal autopsy interview that will be used to categorize the potential cause of death as probable, possibly, or not malaria related.

#### 8.7.6 **Adherence to study intervention protocol and strategies for retention**

##### 8.7.6.1 Adherence to study protocol and medication

At 2, 6 and 10 weeks mothers will be asked to administer already received PMC drug or asked to come to the clinic to receive the drugs. At discharge all mothers regardless of the arm they have been randomised to will be instructed on how to administer DHA to their child. Nurses will demonstrate this by using dummy tablets (placebos) and later the mothers will be asked to do it under supervision. Mothers will be given adequate time to ask for any clarifications during this process. Mothers will also be informed to report to the hospital for any adverse events that the child might experience whether they suspect they are related or not to the study drug.

At discharge, after randomisation, all mothers will be informed of the dates for PMC. These dates will be written in the child's Health Passport and they will additionally be provided with a laminated study card which will contain the Study ID of the child, Name of the child and PMC-1, PMC-2 and PMC-3 dates.

#### 8.7.6.2 Strategies for retention

During screening, parents will be asked whether the child will travel out of the study area for an extended period during the follow-up period. Those who plan 1 month or more away from the study catchment area will be excluded from enrolment.

Detailed directions to the children's homes as well as contact information, including mobile phone information, will be recorded prior to discharge. If children do not return for the Study End visit at 15 weeks, the study team will call them and ask them to come to the clinic for evaluation, offering transport reimbursement, or may visit their house to help arrange transport to the clinic if they are willing to come to the clinic, or, alternately, a study staff may go to their home for Study End visit evaluation.

The caretaker and participant's travel costs will be reimbursed.

#### 8.7.7 Prior and concomitant therapy

All concomitant medications taken during the study will be recorded in the appropriate sections of the CRF with indication, dose information, and dates of administration.

##### 8.7.7.1 Permitted Medications during follow up period

During the treatment and follow-up phase of the study if a subject is diagnosed with malaria the investigator will prescribe antimalarial treatment based on the severity of the malaria illness.

Use of cotrimoxazole (which has some antimalarial properties) treatment or prophylaxis is not considered prohibited as short-courses are commonly prescribed for the treatment of bacterial infection. Daily cotrimoxazole prophylaxis is used by HIV-infected and exposed children.

##### 8.7.7.2 Concomitant and prohibited Medications

Participants will be counselled to avoid concomitant and prohibited medications, specifically antimalarial drugs not prescribed within the trial protocol, or drugs that may be associated with QTc prolongation.

##### *Prohibited medication*

- Antimalarials not prescribed by the study: Chloroquine, halofantrine, mefloquine
- Diuretics (hydrochlorothiazide, furosemide)
- Drugs known to prolong the QT interval
- Antimicrobials:
  - macrolides (e.g. erythromycin, clarithromycin, azithromycin, roxithromycin),
  - fluoroquinolones (e.g. ciprofloxacin, norfloxacin, levofloxacin, moxifloxacin, sparfloxacin)
  - pentamidine
- Antifungals: ketoconazole, fluconazole, Itraconazole, posaconazole, voriconazole, caspofungin
- Antiretrovirals: ARVs, specifically: indinavir, nelfinavir, atazanavir, saquinavir
- Antiarrhythmic agents (e.g. amiodarone, sotalol)
- Non-sedating antihistamines (astemizole, terfenadine)
- Antipsychotics (neuroleptics): Haloperidol, Thioridazine
- Antidepressants: Imipramin, Citalopram, Escitalopram

- Antiemetics: Domperidone, Chlorpromazine, Ondansetron

Randomised participants, who take prohibited medications resulting in the premature cessation of the study intervention, will remain in the trial and will be included in the primary, intention-to-treat analysis, but excluded from the per-protocol analysis.

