## 8.8 PARTICIPANT WITHDRAWAL

Patients can discontinue from the study for any one of the following reasons.

1. Screening error resulting in incorrect enrolment (found that subject did not meet required inclusion / exclusion criteria)
2. Withdrawal of consent at any stage or subject not willing to continue in the study / voluntary discontinuation by the subject
3. Suspected or confirmed allergic reaction to the study drug (removal from therapy only)
4. Safety reasons as judged by the investigator, study safety monitor or DMEC (removal from therapy only)
5. Other

The parents or guardian of subjects who discontinue from the study treatment or from the study entirely will always be asked about the reason(s) for their discontinuation and the presence of adverse events. If a subject discontinues it should be established whether the subject:

1. Discontinues the study treatment, but continues their consent for the data capture up to that point, and to continue follow-up. These subjects will be considered 'off study drug/on study' and where feasible will follow the same schedule of events as those who continue the study intervention, except any adherence assessment. All of these children will be followed until study end at 6 months from enrolment.
2. Discontinues all future activities in the study, but continues their consent for the data captured up to that point to be used in the research
3. Discontinues all future activities in the study and withdraws consent for any data captured to be used for the research

Every effort will be made to follow-up patients who discontinue due to drug related adverse events in order to determine the final outcome. If a subject discontinues due to drug-related adverse events, all the assessments will be conducted that would have been carried out at the next scheduled visit at 6 month (unless consent is withdrawn). This will be recorded in the Case Record Forms (CRFs). The study drug will be returned by the subject. Subjects that have discontinued the study prematurely will not be replaced.

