## 8.9 OUTCOMES

### 8.9.1 Primary Outcome

The primary outcome is the 100% of PMC drugs uptake (defined as administration of **all** 3-day treatment courses, given 2, 6 and 10 weeks after discharge) assessed by unannounced spot checks.

The PMC uptake will be assessed through a study questionnaire administered at unannounced spot checks to determine if and when children and their mothers/guardians attend the scheduled dosing of the drug. The spot checks will be conducted at day 4 or 5

of each DHP treatment course. The effectiveness of the delivery mechanism will be determined by the following measures:

1. **Pill count:** Research Assistants will perform a pill count of the drugs available at the day of the visit. This will be used to assess whether participants took the whole course of DHP or not.
2. **Interview:** A face-to-face interview with the mothers/guardians of children participating in the study will be done to collect information on missed doses and possible reasons for any missed doses.

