### 8.9.2 Secondary Outcomes

#### 8.9.2.1 Adherence outcomes

1. 60% of PMC drugs (defined as administration of 6 or more [but less than 9] of the daily dosages out of the total of 9, given 2, 6 and 10 weeks after discharge
2. 30% of PMC drugs (defined as administration of 3 or more [but less than 6] of the daily dosages out of the total of 9, given 2, 6 and 10 weeks after discharge
3. <30% of PMC drugs (defined as administration of less than 3 of the daily dosages out of the total of 9, given 2, 6 and 10 weeks after discharge

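### The only per-protocol exclusion the protocol states removes only children who fail the primary outcome, so per-protocol uptake would sit at or above intention-to-treat uptake by construction

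*Protocol*

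**What the plan says.** **The exclusion.** The text closing the prohibited-medication list in section 8.7.7.2 concerns "Randomised participants, who take prohibited medications resulting in the premature cessation of the study intervention". These children stay in the trial and "will be included in the primary, intention-to-treat analysis, but excluded from the per-protocol analysis". No other sentence in the protocol defines a per-protocol set. Section 11.7.4 (Data Analysis) names no analysis sets.

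**The outcome.** Section 8.9.1 begins: "The primary outcome is the 100% of PMC drugs uptake". It defines this as giving every 3-day course at 2, 6 and 10 weeks. Section 8.9.2.1 sets the next category down as "60% of PMC drugs (defined as administration of 6 or more [but less than 9] of the daily dosages out of the total of 9". Full uptake therefore means 9 of 9 doses, and 8 of 9 is not full uptake.

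**Other stopping.** Section 8.8 lists further reasons for leaving treatment (allergy, safety, withdrawal of consent, other) and does not name them as per-protocol exclusions. Children who are off the drug but still in the study, where feasible, "will follow the same schedule of events as those who continue the study intervention, except any adherence assessment".

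**The concern.** A per-protocol analysis is normally read as a check on the primary result: if the two agree, the reader gains confidence. That works when the reason for exclusion is distinct from the outcome. Here completing treatment is the outcome, and the exclusion is triggered by not completing it. A child who took a prohibited drug and still finished all nine doses is not excluded by this sentence; a child who took the same drug and stopped is. The set is thus selected on the outcome, in one direction.

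At stake is the reading of a supplementary uptake figure that can only equal or exceed the primary one. It could be presented to policy makers as corroboration when part of its value comes from removing failures from the denominator.

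**Working it through.** **1. Inputs**
- Success: 9 of 9 doses (8.9.1, 8.9.2.1).
- Excluded from per-protocol: only children whose prohibited medication led to early stopping (8.7.7.2).
- Planning uptake: 50% and 75% (8.3).
- Share stopped for this reason, f: not given. Assumed range 2% to 10%, which is 1.5 to 7.5 children in an arm of 75.

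**2. The plan's own figure.** The protocol gives no per-protocol uptake to reproduce. Its sample size (8.3) can be reproduced, and the exclusion does not enter it:
- Unpooled variance, two-sided 5%, 80% power: n = (1.96 + 0.8416)² × (0.50×0.50 + 0.75×0.25) / 0.25² = 54.9 per arm.
- Design effect: 1 + [(1 + 0.036)×3 − 1]×0.1 = 1.2108, giving 66.5.
- 10% loss: 66.5/0.90 = 73.9, or 24.6 clusters of 3, rounded up to 25 clusters and 75 children, as stated.

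**3. Direction.** Let p be intention-to-treat uptake, with the stopped children counted as failures. Every excluded child is a failure, so the numerator is unchanged and the denominator shrinks by the fraction f:

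per-protocol uptake = p/(1 − f) ≥ p

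**4. Size within one arm**

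| f | p = 50% | p = 75% |
|---|---|---|
| 2% | 0.50/0.98 = 51.0% (+1.0) | 0.75/0.98 = 76.5% (+1.5) |
| 5% | 0.50/0.95 = 52.6% (+2.6) | 0.75/0.95 = 78.9% (+3.9) |
| 10% | 0.50/0.90 = 55.6% (+5.6) | 0.75/0.90 = 83.3% (+8.3) |

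**5. Comparison of two arms**
- Equal f: the factor 1/(1 − f) cancels and the relative risk stays at 0.75/0.50 = 1.50. The risk difference is multiplied by the same factor: at f = 5%, 25.0/0.95 = 26.3 points.
- Unequal f, for illustration only: with 2% in the 50% arm and 10% in the 75% arm, 83.3/51.0 = 1.63; reversed, 76.5/55.6 = 1.38. With true uptake of 50% in both arms and f of 2% v 10%, 55.6/51.0 = 1.09 in place of 1.00. No passage supports any particular split.

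**6. Link to section 8.8.** Step 3 counts the stopped children as failures in the intention-to-treat analysis. Section 8.8 exempts children off the drug from adherence assessment and does not say whether they then count as failures or as missing. If they were treated as missing and dropped, the same p/(1 − f) would apply to whatever fraction was dropped. That is a separate ambiguity, not a consequence of the per-protocol rule, but the same sentence settles it.

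**The case against.** The strongest reply has four parts.

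- **No outcome is named.** Section 8.7.7.2 does not say that uptake will be analysed per protocol. The trial also has mortality, readmission and malaria-visit outcomes (8.9.2.2), for which leaving out children taken off the drug is conventional and does not select on the outcome. A separate analysis plan may complete the definition. This stands, and is why the point is conditional on applying the set to uptake. It does not remove the point: the protocol sets this exclusion directly against the primary intention-to-treat analysis, whose outcome is uptake.
- **The rule is narrow.** A reader might infer that the per-protocol set drops everyone who stops early, or that per-protocol uptake must reach 100% in every arm. The text supports neither. One cause of stopping is named, and nothing extends the exclusion to missed doses.
- **Distortion between arms is not shown.** A reader might infer that the comparison of outpatient (OPD) with discharge delivery is biased, because OPD staff see the child at each course (8.6.2) and could notice a prohibited drug. But only the first dose of each course is given there, no passage describes screening for such drugs at that visit, children in all arms are directed to the study clinic when ill (8.7.5.1), and concomitant drugs are recorded for all (8.7.7). Known need for a prohibited drug is also an enrolment exclusion (8.7.4.4), which should keep f low.
- **The question can be coherent.** Uptake among children whose courses were not interrupted by a prohibited drug separates delivery failure from another cause of stopping. That is fair, but the protocol does not describe the analysis in those terms.

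**Conclusion.** The concern holds in a limited form. The one per-protocol exclusion that the protocol states can remove only primary-outcome failures. Applied to uptake, it gives a figure at or above the intention-to-treat figure, and strictly above it in any arm with some successes and at least one such exclusion. The direction follows from the protocol's own definitions. The size rests on the assumed f of 2% to 10%: 1.0 to 5.6 points at 50% uptake and 1.5 to 8.3 points at 75%.

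A reader might go on to infer that the primary result is compromised. It is not compromised by this rule: these children are kept in the intention-to-treat analysis, and the sample size does not depend on the exclusion. The relative risk, which is the planned effect measure (11.7.4), is unchanged when f is equal across arms.

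**What to change.** - **Sections 8.7.7.2 and 8.8:** state that a child who stops the study intervention, for prohibited medication or any other reason, counts as not having full uptake in analyses of the adherence outcomes. This also settles how children exempt from adherence assessment under 8.8 are counted.
- **Section 8.7.7.2:** state that the prohibited-medication exclusion does not apply to the adherence outcomes. It may remain for the clinical outcomes.
- **Reporting:** give the number stopped for prohibited medication by arm, so that f and any imbalance can be seen.

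The cost is a wording change: no new data, no change to sample size and no change to any treatment rule. What is lost is a supplementary estimate of uptake among children whose course was not interrupted by a prohibited drug.

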## 8.8 PARTICIPANT WITHDRAWAL

Patients can discontinue from the study for any one of the following reasons.

1. Screening error resulting in incorrect enrolment (found that subject did not meet required inclusion / exclusion criteria)
2. Withdrawal of consent at any stage or subject not willing to continue in the study / voluntary discontinuation by the subject
3. Suspected or confirmed allergic reaction to the study drug (removal from therapy only)
4. Safety reasons as judged by the investigator, study safety monitor or DMEC (removal from therapy only)
5. Other

The parents or guardian of subjects who discontinue from the study treatment or from the study entirely will always be asked about the reason(s) for their discontinuation and the presence of adverse events. If a subject discontinues it should be established whether the subject:

1. Discontinues the study treatment, but continues their consent for the data capture up to that point, and to continue follow-up. These subjects will be considered 'off study drug/on study' and where feasible will follow the same schedule of events as those who continue the study intervention, except any adherence assessment. All of these children will be followed until study end at 6 months from enrolment.
2. Discontinues all future activities in the study, but continues their consent for the data captured up to that point to be used in the research
3. Discontinues all future activities in the study and withdraws consent for any data captured to be used for the research

Every effort will be made to follow-up patients who discontinue due to drug related adverse events in order to determine the final outcome. If a subject discontinues due to drug-related adverse events, all the assessments will be conducted that would have been carried out at the next scheduled visit at 6 month (unless consent is withdrawn). This will be recorded in the Case Record Forms (CRFs). The study drug will be returned by the subject. Subjects that have discontinued the study prematurely will not be replaced.

## 8.9 OUTCOMES

### 8.9.1 Primary Outcome

The primary outcome is the 100% of PMC drugs uptake (defined as administration of **all** 3-day treatment courses, given 2, 6 and 10 weeks after discharge) assessed by unannounced spot checks.

The PMC uptake will be assessed through a study questionnaire administered at unannounced spot checks to determine if and when children and their mothers/guardians attend the scheduled dosing of the drug. The spot checks will be conducted at day 4 or 5

of each DHP treatment course. The effectiveness of the delivery mechanism will be determined by the following measures:

1. **Pill count:** Research Assistants will perform a pill count of the drugs available at the day of the visit. This will be used to assess whether participants took the whole course of DHP or not.
2. **Interview:** A face-to-face interview with the mothers/guardians of children participating in the study will be done to collect information on missed doses and possible reasons for any missed doses.

### 8.9.2 Secondary Outcomes

#### 8.9.2.1 Adherence outcomes

1. 60% of PMC drugs (defined as administration of 6 or more [but less than 9] of the daily dosages out of the total of 9, given 2, 6 and 10 weeks after discharge
2. 30% of PMC drugs (defined as administration of 3 or more [but less than 6] of the daily dosages out of the total of 9, given 2, 6 and 10 weeks after discharge
3. <30% of PMC drugs (defined as administration of less than 3 of the daily dosages out of the total of 9, given 2, 6 and 10 weeks after discharge

#### 8.9.2.2 Clinical outcomes

1. all-cause mortality
2. Incidence rate of all-cause hospital readmission
3. Incidence rate of readmissions due to severe anaemia (Hb <5g/dL) or severe malaria (parenteral quinine or artesunate)
4. Incidence rate of non-severe all-cause sick-child clinic visits
5. Incidence rate of clinic visit due to RDT/microscopy confirmed non-severe malaria

#### 8.9.2.3 Cost-effectiveness outcomes

1. cost of delivering the PMC services (providers perspective)
2. cost of receiving the PMC services (patients perspective)

#### 8.9.2.4 Feasibility and acceptability outcomes

1. the acceptability of PMC
2. adaptations to their working practices required to implement PMC
3. perceptions of the feasibility of implementing PMC through different delivery mechanisms

### 8.10 EXPECTED DURATION OF TRIAL

The total duration of the trial for a participating mother/guardian-child pair is 3.5 months. Participant recruitment will occur for 30 months. There will be 4 months of follow-up of the last recruited subject and finally 6 months to complete data analysis and study reporting. The end of trial will be defined as the final assessment of the last participant within the trial, unless additional time is needed for follow-up of a trial-associated adverse event. This new protocol is a continuation of COMREC study P.02/15/1679.

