## 4.2 Narrative Protocol Summary

**Title:** Malaria Chemoprevention with monthly treatment with dihydroartemisinin-piperaquine for the post-discharge management of severe anaemia in children aged less than 5 years in Malawi: A 3-year, single site, parallel-group, five-arm cluster randomised trial of community versus health facility-based delivery mechanisms with or without mobile phone SMS reminders

**Short Title:** Post-discharge Malaria Chemoprevention Delivery (PMC) study

**Background and rationale:** Children hospitalised with severe anaemia in Africa are at high risk of readmission or death within 6 months after discharge. No strategy specifically addresses this post-discharge period. In Malawi, 3 months of post-discharge malaria chemoprevention (PMC) with monthly 3-day treatment courses of artemether-lumefantrine (AL) in children with severe malarial anaemia prevented 31% of deaths and readmissions. The effect was in addition to the effect of insecticide-treated bednets. There is now need to design and evaluate effective delivery mechanism for PMC within the health system.

**Objectives:** The primary objective of the trial is to determine the optimum PMC delivery mechanism by comparing community- versus health facility-based strategies in order to inform policy

**Study Type:** This is a single-centre, matched, cluster randomized, 5-arm, factorial design trial comparing the uptake of PMC-DHP delivered through health facility or community-based approaches with or without SMS/HSA reminders.

**Site:** 90 villages in the catchment areas of Zomba Central hospital in southern Malawi

**Study Population:** Inclusion criteria: convalescent children aged less than 5 years and weighing >5 kg admitted with severe anaemia (haemoglobin <5g/dL / Ht <15%); clinically stable, able to take or switch to oral medication; post-transfusion Hb >5g/dL. Exclusion criteria: blood loss due to trauma, malignancy, known bleeding disorders or sickle cell trait, known hypersensitivity to study drug, known heart conditions, non-resident in study area, previous participation in study, known need at enrolment for prohibited medication and scheduled surgery during the course of the study. HIV infection and cotrimoxazole prophylaxis are not exclusion criteria

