## 8.2 STUDY SITE

90 villages in the catchment areas of Zomba Central hospital in southern Malawi. This hospital participated in previous related studies [1, 2, 6] and is particularly suitable for the delivery trial because of the existing linkages with community based health care providers and rural clinics within their catchment areas. In addition, it is close to the College of Medicine where procurement of study resources will be done.

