## 8.3 SAMPLE SIZE

Although a factorial design will be used, only the main effects of PMC mode of delivery and the “use of SMS/HSA reminders” are of primary interest. There are five arms in total as described above such that each of the four intervention arms will be compared to the control arm (Arm 1: Mother given at discharge without SMS reminder). Each village cluster contributes 2 to 4 children/year on average with severe anaemia. Thus, the cluster sizes vary and we have accounted for this in sample size calculations in order to achieve the number of clusters that would have enough power to detect the desired difference. The sample size calculation has been adjusted in the design effect using the coefficient of variation method [11-13]. This has assumed that the cluster sizes will be uniformly distributed between 2 and 4 children i.e. U[2,4]. This gives a mean cluster size of 3 children per village per year and a standard deviation of cluster sizes of 0.58. Hence the coefficient of variation of cluster sizes (CV) is  $0.58/3 = 0.19$  and  $CV^2 = 0.036$ . Assuming an

intra-cluster correlation coefficient (ICC) of 0.1 and allowing for 10% loss-to-follow-up, a sample size of 25 clusters of an average of 3 children per village (75 children per arm, N=375 overall (for 125 clusters for the 5 arms)) has 80% power to detect a 25% absolute increase in uptake from an estimated 50% in the OPD and delivery at home groups to 75% in the arms supported by SMS reminders ( $\alpha=0.05$ ). The ICC of 0.1 is slightly more conservative than the ICC in a previous trial of delivery approaches for IPTc in the Gambia (0.08)[14].

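### Section 8.3 uses one year's yield per village as the whole cluster size, but 8.10 recruits for 30 months and the site has 90 villages, so the stated 80% power does not describe the recruitment planned

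*Protocol*

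**What the plan says.** Protocol section 8.3 introduces the village yield as a rate: "Each village cluster contributes 2 to 4 children/year on average with severe anaemia". It turns that rate into the cluster size for the design effect: "This gives a mean cluster size of 3 children per village per year and a standard deviation of cluster sizes of 0.58". The result is "a sample size of 25 clusters of an average of 3 children per village (75 children per arm, N=375 overall", with the total given as "for 125 clusters for the 5 arms" and the power as 80% for 50% against 75% uptake. The ICC is 0.1 and the allowance for loss to follow-up is 10%. The target in section 4.1 is also 375.

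Section 8.10 sets the accrual period: "Participant recruitment will occur for 30 months". Section 8.2 describes the site as "90 villages in the catchment areas of Zomba Central hospital in southern Malawi", and sections 4.2 and 8.7.4.2 also give 90.

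Section 11.7.1 starts from the same yearly yield but uses 5 children per cluster, with 102 clusters available and no recruitment period stated. No section links cluster size to recruitment time, caps the number per village, gives the fraction of cases expected to enrol, or says that accrual stops at 375.

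**The concern.** In a cluster trial the design effect depends on how many children each village contributes to the analysis, so the relevant count covers the whole accrual period. Section 8.3 uses the count for one year, while 8.10 plans two and a half. The yield, the recruitment period, the number of villages and the target of 375 then cannot all describe one trial, and it is unclear which plan the 80% belongs to. Two things are at stake: whether the trial as run has the power stated, and whether accrual ends at a number or at a date.

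**Working it through.** **Inputs.** From 8.3: 2 to 4 (mean 3) children per village per year, 25 villages per arm, 125 in all, ICC 0.1, squared coefficient of variation of cluster size (CV²) 0.036, 10% loss, 50% against 75%, alpha 0.05. From 8.10: 30 months, or 2.5 years. From 4.2, 8.2 and 8.7.4.2: 90 villages, or 18 per arm over five arms. Assumed: a two-sided test (8.3 does not say) and the same CV² at every cluster size.

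**Formulas.** Design effect = 1 + ((1 + CV²)m − 1) × ICC, with m the children per village. Effective number per arm = children per arm × 0.9 / design effect. Power is the normal approximation for two proportions. Ranges cover m taken before or after the 10% loss, and pooled or unpooled variance.

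**Step 1: reproduce 8.3.** At m = 3, design effect = 1 + (1.036 × 3 − 1) × 0.1 = 1.21. With unpooled variance, n = (1.960 + 0.842)² × (0.25 + 0.1875) / 0.25² = 54.9. Then 54.9 × 1.211 / 0.9 = 73.9 per arm, which is 25 villages of 3. Power at 75 per arm is 79-82%. The stated figure therefore reproduces at m = 3, and 125 × 3 = 375 is one year of recruitment.

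**Step 2: what the yield brings in 30 months.**
- Per village: 2 × 2.5 = 5 to 4 × 2.5 = 10, mean 7.5.
- In 90 villages: 450 to 900, mean 675.
- In 125 villages: 625 to 1,250, mean about 938.
- Time to 375 in 90 villages: 375 / (90 × 3) × 12 = 16.7 months (12.5 at 4 per year, 25 at 2 per year).

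**Step 3: power for each plan.** For 375 in 90 villages, m = 375 / 90 = 4.17 and the design effect is 1 + (1.036 × 4.17 − 1) × 0.1 = 1.33 (1.29 with m after loss, 3.75). The effective number is 75 × 0.9 / 1.33 = 50.7 per arm (52.4 with m after loss). The other rows follow the same way.

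| Plan | Villages per arm | m | N | Design effect | Power |
|---|---|---|---|---|---|
| Section 8.3 | 25 | 3 | 375 | 1.18-1.21 | 79-82% |
| 90 villages, stop at 375 | 18 | 4.17 | 375 | 1.29-1.33 | 75-78% |
| 90 villages, 30 months, lowest yield | 18 | 5 | 450 | 1.37-1.42 | 80-83% |
| 90 villages, 30 months, mean yield | 18 | 7.5 | 675 | 1.60-1.68 | 88-91% |

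**Step 4: where the shortfall comes from.** Rows 1 and 2 have the same N and differ only in the number of villages, so the loss of about 4 percentage points comes from 90 rather than 125 villages. Recruiting for longer in the same 90 villages raises power, because it adds children faster than it raises the design effect.

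**The case against.** The strongest reply is that 375 is a fixed target and 8.10 gives an expected duration, so 30 months is a calendar allowance with a margin. At the lowest stated yield 90 villages need 25 months, and section 8.11.2 provides for stopping if recruitment is poor. This is a reasonable reading, but 8.10 does not state it. It also leaves 4.17 children per village rather than 3, and power below 80%.

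A second reply is that the yield counts children with severe anaemia, not enrolments. Consent, clinical stability, absence of fever and residence all reduce it (8.7.4.4, 8.7.6.2). Enrolling 375 of 450 to 900 cases means 375/900 = 42% to 375/450 = 83%, which is not implausible. This stands as a limit on the overshoot: 450 to 900 is what follows if every case enrols. But 8.3 itself uses the yield as the enrolled cluster size and gives no enrolment fraction, so the definition still has to be supplied.

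A reader might also infer that 30 + 4 + 6 = 40 months contradicts the three-year trial in the title. It does not. Section 8.10 ends the trial at the last participant's final assessment, so 30 + 4 = 34 months, and the 6 months for analysis and reporting come after.

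**Conclusion.** The point holds. The cluster size in 8.3 is a one-year figure for 125 villages, and it matches neither the recruitment period in 8.10 nor the 90 villages given elsewhere. Power is about 75-78% if accrual stops at 375 in 90 villages and about 88-91% for 30 months at the mean yield. Only 30 months at the lowest yield comes near 80%, and that is with 450 children. These figures rest on 8.3's ICC, CV² and loss, a two-sided 5% test and one pairwise comparison of arms.

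Three stronger readings are not supported:
- That the trial will overshoot its target. This needs every case to enrol and accrual to run past 375, and the protocol states neither.
- That longer recruitment weakens the trial. In 90 villages it does the opposite. A sharp loss would need 75 children per arm drawn from far fewer villages, which no section plans.
- That the true yield must be about 1.7 per village-year. That is 375 / 90 / 2.5, solved backwards from the target, and no section gives it as an observed rate.

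**What to change.** In 8.3, define cluster size as the expected enrolments per village over the whole recruitment period. Use the number of villages actually randomised and, if the yield counts cases, a stated enrolment fraction. Recompute the design effect and power from that. For 375 children in 90 villages the statement would be about 4.17 per village, a design effect of about 1.3 and power of about 75-78%.

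In 8.10, state that accrual closes at 375 and that 30 months is a maximum, or give the duration that follows from the yield (about 17 months in 90 villages, 12.5 to 25, if all cases enrol).

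The cost is a recalculation, some text and a slightly lower stated power. Keeping 80% in 90 villages would need more children. With unpooled variance and m before loss, 18 × m × 0.9 / (0.9 + 0.1036m) = 54.9 gives m of about 4.7, or roughly 85 per arm and 425 in all. Whether to accept the lower power or the larger number is for the sponsor to decide.
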